### Planned data statistical analysis

Statistical analysis will be performed with SPSS 22.0 (SPSS, Inc., Chicago, USA). Baseline characteristics of each stroke center (see Additional file 3) and the patients enrolled will be analyzed. The achieved rates of all KPIs of 30 hospitals during pre-intervention stage and the last 6 months of post-intervention stage are compared by the paired *t* test. KPIs are also collected at multiple time points before and after intervention. Interrupted time series (ITS) analysis is performed to assess the efficiency on outcome 1 year after the intervention is carried out [19, 20]. The multiple time points before the intervention allow the underlying trend to be estimated, and the multiple time points after the intervention allow the intervention effect to be estimated accounting for the underlying trend. No additional adjusted analyses will be performed. All the information to calculate the KPIs was included in the medical records. The missing data not extracted by a computer will be extracted manually by a clinician. There are no anticipated problems that are detrimental to the participant so that there are no formal stopping rules for the trial. The schedule of enrolment, interventions, and assessments is included in Fig. 3.

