## Method and design

### Design

This is an 18-month prospective, multicenter, historical control study among 30 stroke centers in Zhejiang Province, China. Stroke centers with in-hospital stroke patients voluntarily participate in this trial. All medical documents of consecutive AIS patients admitted in the stroke center according to ICD-10 (I63 and G45) are collected by investigators from Zhejiang Stroke Quality Control Center (ZSQCC). Only the de-identified documents are preserved in a safe information database. The clinical data involved in this study belong to the scope of information collection of routine clinical practice. The local infrastructure and characteristics of each recruited center are also recorded. The study protocol is approved by the Institutional Review Board of the Second Affiliated Hospital of Zhejiang University (SAHZU). Because patient information in the CASE is de-identified and anonymized before being released to the researchers, the informed consent requirement is waived by SAHZU Institutional Review Board. All the protocol item is standardized (see Additional file 1). It was registered at ClinicalTrials.gov (NCT03684629).

There are two stages in this trial: pre-intervention stage (the initial 6 months) and post-intervention stage (the next 12 months). We collect the consecutive data of each center during the pre-intervention stage without feedback of KPIs and then monthly send its own KPIs to each center during the post-intervention stage. We finally compare the changes of KPIs from pre-intervention stage to the last 6 months of post-intervention stage (Fig. 1).

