### Sample size

Among all the KPI, the adherence to intravenous thrombosis (IVT) was poor in china [18]. Result of investigation in Zhejiang before the trial indicated that only approximately 8% of ischemic stroke patients received IVT 4.5 h after stroke onset. To detect 10% improvement in the adherence to IVT, with *α* = 0.05 and power = 90%, at least 16,570 patients will be needed in pre-intervention stage and post-intervention stage.

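### The 90% power is stated for a count of patients, but the planned test is a paired t test on 30 hospital rates, so 90% is not shown to be the power of that test

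*Protocol article*

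**What the plan says.** The Sample size section starts from a pre-trial survey in which "only approximately 8% of ischemic stroke patients received IVT 4.5 h after stroke onset". The target is "To detect 10% improvement in the adherence to IVT". Alpha is set at 0.05 and power at 90%, and the result is that "at least 16,570 patients will be needed in pre-intervention stage and post-intervention stage". It does not say whether the improvement is absolute or relative, whether 16,570 is per stage or for both stages together, or which formula was used. It gives no number of hospitals, no SD of hospital rates or of their change, and no intracluster correlation.

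The Design section describes a "historical control study among 30 stroke centers in Zhejiang Province, China". On the comparison itself, the section Planned data statistical analysis states: "The achieved rates of all KPIs of 30 hospitals during pre-intervention stage and the last 6 months of post-intervention stage are compared". The method it names for this is a paired t test. An interrupted time series analysis is also planned, and further adjusted analyses are ruled out.

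**The concern.** A power figure belongs to a particular test. Here the figure is built from patients and one patient-level proportion, while the test has 30 observations, one change per hospital. The error term of the paired t test is the SD of those 30 changes. It has two parts: binomial sampling noise, which shrinks as patients accrue, and true differences between hospitals in how much they change, which do not.

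The second part is unlikely to be zero. The Intervention section tailors education and improvement plans to each centre, and the Discussion accepts that care in individual hospitals may drift over time. If this part is sizeable, the number of hospitals limits the result, and a non-significant IVT comparison could be misread as a negative finding from a study with 90% power.

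**Working it through.** **Inputs from the document.** Base rate 8%; alpha 0.05 (taken as two-sided, since sidedness is not stated); power 90%; 16,570 patients; 30 hospitals; 6 months before compared with the last 6 months after.

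**Assumptions.** Equal patient numbers in the two periods; equal hospital sizes; a between-hospital SD of true change, τ, of 0 to 3 percentage points. The document does not give τ, so a range is shown.

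**Step 1: reproduce 16,570.** For two independent proportions with pooled variance under the null,

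n per stage = [1.960·√(2p̄(1−p̄)) + 1.282·√(p₁(1−p₁) + p₂(1−p₂))]² / (p₂−p₁)², where p̄ = (p₁+p₂)/2.

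| Effect | n per stage | with continuity correction |
|---|---|---|
| 8% to 8.8% (relative 10%) | 25,264 | 25,513 |
| 8% to 18% (absolute 10 points) | 236 | about 255 |
| 8% to 9% (1 point, relative 12.5%) | about 16,342 | 16,542 |

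Neither literal reading of the stated improvement gives 16,570, per stage or as a total. The third row does: the corrected value is within 0.2% (28/16,570) and the uncorrected one within 1.4% (228/16,570). It is a calculation on independent patients.

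**Step 2: power of the planned test.** The SD of a hospital's change is

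SD = √[(p₁(1−p₁) + p₂(1−p₂))/m + τ²],

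with m = 16,570/30 ≈ 552 patients per hospital per stage. Power comes from the non-central t distribution with 29 df and non-centrality (p₂−p₁)·√30/SD.

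For 8% to 9%, the sampling part is √[(0.0736 + 0.0819)/552.3] = 1.68 points.

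| τ (points) | SD of change (points) | Power, 8% to 9% | Power, 8% to 8.8% |
|---|---|---|---|
| 0 | 1.68 | 88% | 72% |
| 1 | 1.95 | 77% | 59% |
| 2 | 2.61 | 53% | 37% |
| 3 | 3.44 | 34% | 23% |

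(The SD column is for 8% to 9%; for 8% to 8.8% it differs by about 0.01.)

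**Step 3: separate the causes.** At 16,570 per stage, a test on independent patients has 90.4% power for 8% to 9% and 74.7% for 8% to 8.8%. At τ = 0, moving to the paired t test therefore costs about 2 points of power in the first case (90.4% to 88%) and about 3 in the second (74.7% to 72%). For 8% to 8.8%, about 15 of the 18 points between 90% and 72% arise because 16,570 does not follow from those inputs. The unit of analysis matters through τ.

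**Step 4: if 16,570 is the total.** With 8,285 per stage (m ≈ 276) and 8% to 8.8%, paired-t power is 43% at τ = 0 and 20% at τ = 3. Independent patients would already give only 46%.

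**Step 5: detectable change.** With 30 pairs, 90% power needs a mean change of about 0.61 SD. At 552 patients per hospital per stage this is 0.61 × 2.61 ≈ 1.6 points at τ = 2 and 0.61 × 3.44 ≈ 2.1 points at τ = 3.

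**The case against.** Several objections have force.

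- **The test is sound.** A paired t test on hospital summaries respects clustering, carries the variation in hospital change in its error term, and removes stable hospital differences. This stands. A reader might infer that the analysis is invalid or must be replaced by a patient-level mixed model. The document does not support that: such a model with a hospital-by-stage effect meets the same limit of 30 hospitals.
- **Direction is not fixed.** A reader might infer that power is overstated on every reading. If the improvement means 8% to 18%, paired-t power is above 99% up to τ of about 10 points and about 94% at 15. But that effect needs only about 236 to 255 patients per stage, so it cannot be the basis of 16,570.
- **Independence is inferred.** The Sample size section names no formula. The inference rests on the missing cluster input and the close match in Step 1.
- **τ is assumed.** No size of loss is established, only how power varies with τ.
- **Equal weighting.** A reader might add that weighting small and large hospitals equally wastes precision. The document gives no hospital volumes, and once hospitals truly differ in their change by 2 to 3 points, equal weighting is close to the best choice. This does not stand as a criticism.
- **Enrolment is consecutive over fixed periods.** The figure is stated as a minimum, so 552 per hospital per stage is a floor. More patients reduce sampling noise but leave τ unchanged.

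The interrupted time series is a separate analysis, and the Sample size section does not tie its power to it.

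**Conclusion.** The concern holds as a defect of the power statement. The 90% has no hospital-level input and is not the power of the paired t test on 30 hospital rates. For the effect that reproduces 16,570 (8% to 9%, per stage), planned-test power is 88% at best with the stated minimum number of patients, and 77%, 53% or 34% at τ of 1, 2 or 3 points. For 8% to 8.8% it runs from 72% to 23%, but most of the shortfall at τ = 0 comes from a sample size that does not follow from its inputs. These figures assume two-sided 5% testing, equal hospital sizes, equal stages and the assumed range of τ. The defect does not bias the estimate or invalidate the test.

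**What to change.** In the Sample size section, state whether the improvement is absolute or relative, whether 16,570 is per stage or total, and which formula was used. Then restate power, or the change detectable with 90% power (about 0.61 SD), for 30 hospital pairs over a range of SDs of hospital-level change. That range should be informed, if possible, by month-to-month variation within hospitals in the pre-intervention stage. Those months cannot show how much hospitals differ in their response to the intervention, so a range is still needed.

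The paired t test may stay. A patient-level logistic mixed model with hospital and hospital-by-stage effects is optional.

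The cost is a recalculation and a few sentences, with no new data collection. The downside is that the quoted power becomes less favourable.

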### The inclusion criteria for the analysis of medical documents

Patients 18 years or olderAIS confirmed by computed tomography (CT) or diffusion-weighted imaging (DWI)Admitted within 7 days from symptom onset

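### The plan rules out adjustment beyond the interrupted time series, so a change in patient mix that begins with or after the intervention enters both effect estimates

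*Protocol article*

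**What the plan says.** The Design section describes the study as follows: "This is an 18-month prospective, multicenter, historical control study among 30 stroke centers in Zhejiang Province, China". The stages are "pre-intervention stage (the initial 6 months) and post-intervention stage (the next 12 months"), and the contrast of interest is also set there: "We finally compare the changes of KPIs from pre-intervention stage to the last 6 months of post-intervention stage".

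Planned data statistical analysis names two effect analyses. In the first, the hospitals' KPI rates "during pre-intervention stage and the last 6 months of post-intervention stage are compared by the paired *t* test". The second is an ITS, for which "the multiple time points after the intervention allow the intervention effect to be estimated accounting for the underlying trend". The next sentence is the rule at issue: "No additional adjusted analyses will be performed".

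The same section says "Baseline characteristics of each stroke center (see Additional file 3) and the patients enrolled will be analyzed", but neither effect analysis is described as using those characteristics. Entry is open to any patient who meets the criterion "Admitted within 7 days from symptom onset". The Discussion concedes that a hospital's quality of care may change over time; it does not mention a change in the kind of patient admitted.

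**The concern.** The two stages contain different people, and nothing was randomised between stages. Pairing by hospital removes what is constant about a hospital. It does not remove a change over time in who that hospital admits. With a 7-day admission window, the split between early and late arrivals, or the age distribution, can move between stages and shift some KPI rates while care stays the same.

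After secular trend, this is the main threat to a historical-control comparison. The plan does not leave the matter open: it states a decision against further adjustment, and a separate analysis plan that adjusted for case mix would contradict it. At stake is whether an improvement in a primary KPI can be credited to feedback and education rather than to a different intake.

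**Working it through.** **1. The plan's own figures.** The Sample size section gives a base thrombolysis rate of about 8% of ischemic stroke patients, a 10% improvement, alpha 0.05, power 90% and 16,570 patients. It does not say whether 10% is relative or absolute, whether the test is one- or two-sided, or whether the number is per stage. Two-sided two-proportion calculations, per stage:

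| Change | n per stage |
|---|---|
| 8% to 8.8% (10% relative) | 25,264 |
| 8% to 18% (10 points) | 236 |
| 8% to 9% (1 point) | 16,343; 16,542 with continuity correction |

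The stated number is not reproduced under either reading of 10%; the nearest match is a 1-point change. That mismatch is a separate matter. What counts here is that the effect the trial is sized for appears to be about 1 point, so a small artefact would be of the same order.

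**2. How each analysis responds to a pure mix change.** Assumptions: 18 monthly points (6 before, 12 after), no noise, no true effect, and a mix change scaled to raise the mean of months 13–18 above the mean of months 1–6 by 0.8 points. ITS model: rate = intercept + time + level change at month 7 + slope change from month 7. The ITS effect at month 18 is level change + 12 × slope change.

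| Mix change | Paired difference | ITS effect at month 18 |
|---|---|---|
| Step at month 7 | +0.8 | +0.8 |
| Steady linear drift over all 18 months | +0.8 | 0.0 |
| Linear drift starting at month 7 | +0.8 | +1.0 |

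In the last row the mean time since month 6 in the final window is (7 + … + 12)/6 = 9.5 months. The monthly slope is 0.8/9.5 = 0.0842, and 12 × 0.0842 = 1.01.

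The paired test takes in the mix change in full in all three cases. The ITS removes it only when the drift was already running, linearly, before the intervention.

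**3. How firmly the ITS trend is estimated.** With independent monthly errors of standard deviation 1, the standard error of the ITS effect at month 18 is 3.53. For a difference of two 6-month means it is √(2/6) = 0.58. The protection that the ITS offers rests on a long extrapolation from 6 points.

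**4. Size of shift needed, for thrombolysis.** Assumption: only in-window arrivals can be treated, and the denominator is all ischemic stroke patients, as in the Sample size section. The documents give no in-window share, so a range is shown. The treated fraction is 0.08 / share, and the share that yields 8.8% is 0.088 / treated fraction.

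| In-window share | Treated among them | Share giving 8.8% | Shift |
|---|---|---|---|
| 20% | 40% | 22% | 2 points |
| 25% | 32% | 27.5% | 2.5 points |
| 30% | 26.7% | 33% | 3 points |
| 40% | 20% | 44% | 4 points |

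For the second row: 0.25 × 0.32 = 0.080 and 0.275 × 0.32 = 0.088.

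**5. The other denominator.** If the KPI is computed among in-window patients, the second row gives 32% in both stages, so this shift does not bias it at all.

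**The case against.** A reader might infer that the plan forbids all adjustment, and that any change in patient mix goes straight into every effect estimate. The documents do not support this. The sentence excludes additional adjusted analyses directly after describing an ITS that adjusts for trend, and the ITS gives 0.0 under steady drift. The unlimited statement is true only of the paired test.

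A reader might also take the move from 8.0% to 8.8% as a forecast of bias. It is not. The shares are assumed, the arithmetic says nothing about how likely such a shift is, and the KPI formula is in Additional file 2, which is not shown. Thrombolysis is also a favourable example: the anticoagulation KPI, for instance, is already limited to patients with atrial fibrillation.

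Several design features limit mix change, and they stand. The same hospitals are compared, patients are consecutive, and eligibility is the same in both stages. From the mid-August 2018 start in Trial status, both 6-month windows run roughly from mid-August to mid-February, 12 months apart, so seasonal mix is largely balanced in the paired contrast.

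Adjustment has its own hazard, and this too stands. A quality programme may change how comorbidities are detected and documented, so adjusting for them could add bias. Nor do the documents list every field that is extracted.

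None of this gives the paired test any control for a within-hospital change in patients, or lets the ITS remove a change that starts with the intervention. The historical-control limitation that the Discussion concedes concerns quality of care, not intake.

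**Conclusion.** The point holds in limited form. The paired t test has no case-mix adjustment. The ITS corrects only for the trend seen in 6 pre-intervention months, and the plan excludes anything further. A change in mix that starts with or after the intervention therefore passes into both estimates: for a change worth 0.8 points in the paired contrast, +0.8 in the ITS if it is a step at month 7 and about +1.0 at month 18 if it is a drift from then. A steady drift that was already running affects the paired test only.

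The thrombolysis illustration depends on an all-patient denominator and on assumed shares. Over an assumed in-window share of 20% to 40%, a rise of 2 to 4 points reproduces a 10% relative improvement; with an in-window denominator the bias is nil. The documents do not show that such a shift occurred or is likely. The flaw is that the plan excludes the analysis that would check for it.

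**What to change.** Replace the sentence that excludes further adjusted analyses with a pre-specified case-mix-adjusted analysis of each primary KPI, reported beside the planned paired t test and ITS.

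- **Model:** patient-level logistic regression with hospital effects and either a stage term or the ITS time terms.
- **Main covariates:** a fixed set, limited to fields actually extracted and unlikely to be recorded differently because of the intervention. Age and time from onset to admission are natural choices, since eligibility depends on both; add sex if it is extracted.
- **Further sensitivity analysis:** add comorbidities such as atrial fibrillation, hypertension and diabetes here only, because their documentation may improve under the programme.
- **Avoid:** reliance on the recorded NIHSS. Its completion is itself a primary KPI, so its missingness is likely to differ by stage.

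The cost is an amended passage and some extra analysis for seven KPIs, on patient characteristics of which at least some will be analysed anyway. Confounding by unrecorded factors would remain, and the report should say so.

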### Intervention for medical care improvement

Individualized quality improvement process is divided into 3 steps:
Each stroke center receives their own KPIs monthly, as well as the average KPI level of all 30 stroke centers as contrast, which are automatically calculated by computer analyzing system.Based on the performance of KPI data, stroke experts from ZSQCC identify the items which need to be improved, provide each center with relevant education of guidelines, and help the clinicians to examine the causes of non-compliance of guideline-based care and develop programs to decrease their frequency via regular teleconference per month and face-to-face lectures quarterly. In the meantime, stroke centers with the best KPI performance also share their experiences on medical care improvement.Each stroke center is then required to provide a detailed improvement plan for each KPI and check whether it is implemented one by one during the next teleconference.

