### Outcome

The primary outcomes are as follows: 7 KPIs including the accomplishment of National Institutes of Health Stroke Scale (NIHSS), intravenous thrombosis within 4.5 h of onset, antiplatelet agent therapy within the first 48 h, statin use after hospitalization and at discharge, antithrombotic therapy at discharge, and anticoagulant treatment for patients with atrial fibrillation at discharge [8, 9, 11–13] (see Additional file 2).

The secondary outcomes are as follows: 9 KPIs including prevention of deep vein thrombosis, blood vessel evaluation within 1 week of hospitalization, swallowing function evaluation, blood lipid level assessment, rehabilitation evaluation and implementation, recommendation of life style change, anti-hypertensive therapy, hypoglycemic treatment at discharge, and recurrence rate [10, 11, 17] (see Additional file 2).

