### Trial management and monitoring

The Trial Management Group (TMG) will be responsible for all aspects of local organization and the day-to-day running of the trial, including monitoring the operation and maintenance of the computer analyzing system, outcome data collection, and ensuring the feedback of KPIs to the relevant hospitals every month. The trial will be overseen by an independent Trial Steering Committee (TSC), which will meet at least monthly to consider and address strategic issues. A Data Monitoring Committee (DMC), members of which will act independently of the TSC, TMG, and funder, will monitor data, check the quality of extracted data, and make recommendations to the TSC on whether there are any ethical or safety reasons why the trial should not continue. The serious adverse events (SAEs) which will be recorded and reported in this trial are deaths by any cause in the 1 year after hospitalization. The DMC will monitor the occurrence of SAEs. Patient information in the CASE is de-identified and anonymized, extracted from medical document after discharge.

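### Safety recording stops at death, although four of the seven primary KPIs are meant to raise treatments that carry bleeding risk and no KPI measures bleeding

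*Protocol article*

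**What the plan says.** All references are to the protocol article.

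- *Planned data statistical analysis* gives the premise on harm: "There are no anticipated problems that are detrimental to the participant so that there are no formal stopping rules for the trial".
- *Trial management and monitoring* fixes what counts as a safety event. The SAEs are those "which will be recorded and reported in this trial are deaths by any cause in the 1 year after hospitalization". The DMC monitors these SAEs and has a general remit to advise on ethical or safety reasons not to continue.
- *Outcome* names every KPI. The seven primary ones include "intravenous thrombosis within 4.5 h of onset, antiplatelet agent therapy within the first 48 h" and "antithrombotic therapy at discharge, and anticoagulant treatment for patients with atrial fibrillation at discharge". The other three are NIHSS completion and statin use at two time points. The nine secondary ones begin with "9 KPIs including prevention of deep vein thrombosis, blood vessel evaluation within 1 week of hospitalization". Recurrence rate is the only clinical outcome among the 16.
- *Intervention for medical care improvement* describes how the rates are to be moved: monthly feedback against the 30-centre average, expert education, and a further obligation: "Each stroke center is then required to provide a detailed improvement plan for each KPI".

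**The concern.** The premise that nothing detrimental is to be expected does not sit well with an intervention whose purpose includes more thrombolysis, more antiplatelet treatment and more anticoagulation. These treatments carry bleeding risk even when they are well indicated. The safety definition leaves that risk out unless it kills, and then records it as a death without a cause.

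A patient who receives IVT and then has a non-fatal intracranial haemorrhage contributes to the IVT KPI and to no safety count. A higher IVT or anticoagulation rate could thus be reported as better care, and proposed for wider use as the *Conclusion* envisages, with no information on what happened to bleeding over the same period. The DMC is asked for safety advice, but death is the only safety event defined for it.

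This is not detail that an article leaves to a fuller document. The article itself states the premise, closes the SAE definition and lists the outcomes.

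**Working it through.** **1. Count of outcomes (*Outcome*)**

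- Primary KPIs that raise thrombolytic or antithrombotic use: IVT within 4.5 h, antiplatelet within 48 h, antithrombotic at discharge, anticoagulant in atrial fibrillation. That is 4 of 7.
- KPIs that measure bleeding: 0 of 7 + 9 = 16.

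**2. The plan's own figure (*Sample size*)**

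Inputs: about 8% IVT before the trial, a 10% improvement (relative or absolute not stated), α = 0.05, power 90%, at least 16,570 patients (per stage or in total not clear). With the usual two-proportion formula, two-sided,

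n per stage = [1.96·√(2p̄q̄) + 1.2816·√(p₁q₁ + p₂q₂)]² / (p₂ − p₁)²

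- 8% to 8.8% (10% relative): 25,264 per stage.
- 8% to 18% (10 points): 236 per stage.
- 8% to 9%: 16,343 per stage, or 16,542 with continuity correction.

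The stated 16,570 does not reproduce under either reading of 10%. It lies close to a one-point rise, counted per stage. That mismatch is a separate matter. Here it shows only that the 18% reading does not fit the planned size, so I use the relative reading and take either 8,285 or 16,570 patients in each of the two periods compared.

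**3. Extra IVT patients and extra haemorrhages**

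Assumption, not in the documents: 2% to 6% of patients given IVT have a symptomatic intracranial haemorrhage.

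| Patients per period | IVT at 8% | IVT at 8.8% | Extra treated | Extra events at 2% | Extra events at 6% |
|---|---|---|---|---|---|
| 8,285 | 663 | 729 | 66 | 1.3 | 4.0 |
| 16,570 | 1,326 | 1,458 | 133 | 2.7 | 8.0 |

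(Extra treated = N × 0.008, before rounding.) For the 9% target that nearly returns the plan's figure, 16,570 × 0.01 = 166 extra treated, and 166 × 2% to 6% = 3 to 10 events, the same order. Bleeding from antiplatelet or anticoagulant treatment is not in these counts.

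**4. What a before-after comparison could show**

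Assume a 4% rate among treated patients in both periods and ignore clustering in 30 centres:

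half-width of 95% CI = 1.96·√[0.04 × 0.96 × (1/n₁ + 1/n₂)]

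- 663 against 729 treated: 2.06 points.
- 1,326 against 1,458 treated: 1.46 points.

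Power to detect the rise in haemorrhages over all patients is below 10% on the 8.8% reading, in every variant run (2%, 4% or 6% risk in treated patients, 0% or 0.5% in the rest).

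**5. Whether the data are there**

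*Design* says all medical documents of consecutive patients are collected. *Data monitoring and confidentiality* says the hospital-stay record is saved, extracted by software and traceable to the source for checking. In-hospital bleeding noted in those records could therefore be extracted for both stages.

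**The case against.** The case on the other side is substantial, and parts of it stand.

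- **Bleeding is not wholly unseen.** All-cause death is recorded, so fatal bleeds are counted. This stands: what is lost is non-fatal bleeding and the attribution of deaths.
- **A reader might infer that the trial would be declared a success while bleeding rose.** The article states no success rule. It describes a paired *t* test and an interrupted time series on the KPIs. What can be said is only that a KPI gain would carry no bleeding data with it.
- **A reader might infer that benchmarking would push centres into treating unsuitable patients.** The article does not support this. The intervention is education towards guideline care, and the KPI definitions, including any exclusions, are in Additional file 2, which is not shown.
- **A reader might take the 10% as ten points and arrive at 17 to 99 extra haemorrhages.** That needs a rise from 8% to 18%, which would call for 236 patients per stage and does not fit 16,570.
- **The DMC may see more than deaths.** Its remit is general and the article does not list its reports. The firm gap is the SAE definition.
- **A bleeding rate alone does not show net harm.** Some extra bleeding can accompany appropriate extra treatment, and a rate per treated patient would not show events that arise simply because more patients are treated. This stands, and is a reason to report counts as well as rates and to present them descriptively.
- **Extraction is not trivial.** The reported 3.4% inconsistency between software and manual extraction is of the same order as the assumed 4% event rate, so manual checking would have to carry the measure.

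None of this removes the central point: the stated premise and the closed SAE definition do not match what four of the primary KPIs are meant to increase.

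**Conclusion.** The concern holds in a limited form. The KPI estimates themselves are not invalidated. What is affected is safety monitoring and what a KPI gain can be taken to mean.

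On the relative reading the IVT-related excess is about 1 to 8 symptomatic intracranial haemorrhages, and a comparison of rates among treated patients could exclude only a large deterioration, given its half-width of about 1.5 to 2.1 points. These sizes rest on an assumed 2% to 6% risk (4% for the interval), on equal numbers in the two periods, on 8,285 or 16,570 patients per period, and on no clustering, which would probably widen the interval. The counts in step 1 of the working need no assumption. The change is worth making because it is cheap relative to what it adds, not because a large harm has been shown.

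**What to change.** Reconcile *Outcome*, *Planned data statistical analysis* and *Trial management and monitoring*:

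1. Remove the statement that no detrimental problems are anticipated.
2. Add two descriptive balancing safety outcomes, each with a prespecified definition: in-hospital symptomatic intracranial haemorrhage after IVT (denominator: patients given IVT) and major in-hospital bleeding (denominator: all analysed patients).
3. Extract both from the records already collected, with the existing investigator check.
4. Report counts and rates with confidence intervals for the pre-intervention stage and the last 6 months, give them to the DMC, and present gains on the antithrombotic KPIs beside them.

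Cost: a protocol amendment, a few more fields to extract and check by hand, and one extra table. Bleeding after discharge remains unseen. No treatment or stopping rule is proposed; treatment decisions stay with the centres.
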